### Study procedures and measurements

Participants will be monitored over a 12-week period each year during the harvest season, which coincides with the rainy season in both the Nouna and Siaya HDSS sites, for a duration of three consecutive years. This repeated seasonal monitoring enables the collection of longitudinal data on heat exposure, work capacity, and agricultural productivity, capturing both seasonal dynamics and interannual variability.

At baseline, field workers will collect socio-demographic information using structured questionnaires implemented via Survey Solutions (https://mysurvey.solutions/en/). The digital platform includes multi-level plausibility checks to enhance data quality. Data will be collected using tablets and uploaded directly to the Survey Solutions server either from the field or HDSS offices. Supervisors will review submissions for completeness and consistency; if discrepancies or missing values are identified, forms will be returned to field workers for verification and correction prior to final approval.

Before the onset of participant monitoring, field workers will measure the perimeter of each farmer’s plot and record the types of crops cultivated. These data will be integrated into remote sensing models to support the estimation of harvest yields and agricultural productivity [31].

Participants aged 18 years and older will be equipped with wearable devices (see Chapter 2.4.1 onwards for further details) that continuously monitor heart rate, physical activity, and sleep patterns throughout the study period. These devices will generate high-resolution data on physiological strain, behavioral activity, and recovery dynamics in response to heat exposure, enabling detailed analysis of the relationship between thermal stress and work capacity. Participants are instructed to wear the devices continuously, with data synchronized via the Fitrockr application (https://www.fitrockr.com/). Due to limited smartphone access among participants, field workers will oversee data synchronization using tablets to ensure regular uploads and minimize data loss.

Complementing the wearable monitoring, each participant will carry a GPS tracker for a minimum of 20 days annually during the harvest season. The GPS devices will capture spatial and temporal work patterns, including fieldwork duration and distance traveled, offering granular insights into labor exposure under varying thermal conditions. Data from GPS units will be stored locally and synchronized offline by field staff at predefined intervals.

To ensure uninterrupted device operation, participants will be provided with power banks for overnight charging. Additionally, foldable solar panels will be supplied to allow direct charging of devices or recharging of power banks as needed.

#### Heat (health impact pathway 1)

##### Indoor air temperature and humidity

Indoor air temperature and relative humidity will be recorded at 15-minute intervals using iButton DS1923 hygrochron and SwitchBot Thermometer & Hygrometer sensors. Additionally, to validate these readings, a portable Wet Bulb Globe Temperature (WBGT) device (PCE-WB20SD, Germany) will be deployed in a subset of households. WBGT is primarily used for outdoor environmental heat stress assessments at workplaces; however, in this study, it will serve as a complementary tool to verify indoor heat conditions.

##### Outdoor weather metrics

The Nouna and Siaya HDSS areas each have five automatic weather stations that have been operational since mid-2020 (as depicted in Figure 4). These stations continuously record meteorological parameters, including:
Air temperatureRainfallWind speed and directionSolar radiation

**Figure 4. f0004:**
[figure not shown]
Automated weather station with General Packet Radio Service (GPRS) connectivity located within the Nouna Health and Demographic Surveillance System (HDSS) site, recording real-time data on rainfall, temperature, wind speed and direction, and solar radiation.

These data points are updated every 15 minutes and transmitted in real time via a General Packet Radio Service (GPRS) system, ensuring immediate remote access for analysis. The recorded data is stored on a dedicated server, which also provides a dashboard for visualization (for specific locations of weather stations, see reference [45].

#### Physiological response and work capacity (health impact pathway 2)

To monitor farmers’ physiological responses to heat exposure, the study will deploy two types of wearable devices to enable continuous, high-resolution data collection. All participants will wear the Garmin Vivosmart 5, which records heart rate, step count, and sleep metrics, including duration and quality. This device will be worn throughout the study period to provide real-time data on physiological strain. Additionally, a subset of participants will wear the Activinsights GENEActiv Original, a high-resolution actigraphy device that records gross motor activity and sleep at 10 hz, providing complementary data to the Vivosmart 5. To distinguish between heart rate changes due to physical exertion and those due to heat exposure, the analysis will incorporate methodological corrections, including adjustments for cardiac drift.

To assess work capacity, daily activity, and rest behavior, the study will monitor key indicators such as time engaged in fieldwork, distance traveled, and frequency and duration of rest periods. Each participant will use a Renkforce GP-102 Porter GPS tracker for a minimum of 20 days during the harvest season, capturing spatial and temporal data on labor patterns. GPS data will be stored locally and synchronized offline by field workers at scheduled intervals.

Prior to deployment, compatibility testing will be conducted to ensure that concurrent use of multiple wearable devices does not result in signal interference. Charging logistics will be optimized by providing participants with power banks and foldable solar panels, enabling overnight charging and minimizing disruptions to continuous data collection.

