**What is the impact of heat exposure on the physiological responses of farmers?**
**Hypothesis 1**: Increased heat exposure will significantly elevate physiological strain, as measured by heart rate and body temperature.**How does heat exposure influence farmers’ work capacity and farming behaviors?**
**Hypothesis 2**: Higher temperatures will reduce work capacity and alter farming behaviors, including daily activity patterns, sleep quality, duration, and energy expenditure.**What is the relationship between heat exposure, work capacity, health, and farming practices on harvest yields?**
**Hypothesis 3**: Heat exposure will lead to reduced harvest yields by impairing farmers’ work capacity and health.**How do these factors indirectly affect the nutritional status of children under five in farming households?**
**Hypothesis 4**: Reduced work capacity and lower harvest yields due to heat exposure will negatively impact child nutrition.

This study systematically investigates these pathways using wearable sensors, GPS tracking, offering valuable insights into climate-related challenges faced by subsistence farmers and their families.

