## Methods

### Health impact pathways of heat on physiological response, agricultural capacity, harvest yield, and nutritional status of children

The first health impact pathway examines physiological strain due to heat exposure, incorporating temperature, humidity, and the Wet Bulb Globe Temperature (WBGT) index. The WBGT is a standardized composite index that quantifies environmental heat stress by integrating multiple meteorological parameters, including air temperature, relative humidity, and solar radiation. It serves as a physiologically relevant proxy for the subjective perception of heat, capturing the cumulative thermal load experienced by the human body under varying environmental conditions, and is widely employed to assess the potential impact of heat on physical performance and safety. As WBGT levels increase, physical work capacity declines, with significant reductions observed at 27–28°C WBGT [38,41,42].

The second health impact pathway examines the relationship between heat exposure, physiological responses, and work capacity. Prolonged exposure to heat increases cardiovascular strain (above ~26–27°C cardiovascular strain can begin to increase), exacerbates pre-existing health conditions, and heightens the risk of heat-related illnesses, including heat stress, heat stroke, and renal failure. These health effects contribute to reduced work performance, affecting the duration and intensity of agricultural labor. Given that heart rate fluctuations result from both physical exertion and heat stress, careful methodological adjustments will be made to differentiate between these factors (e.g., accounting for cardiac drift in wearable device data).

The third health impact pathway examines how heat affects agricultural work capacity, particularly during peak farming periods such as harvesting. Heat exposure may lead to shortened work shifts, more frequent rest breaks, and reduced overall labor productivity, ultimately impacting both crop yields and harvest quality. This pathway investigates the interplay between heat stress, labor dynamics, and agricultural output, while accounting for variations in socioeconomic conditions, farming techniques, and land use.

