### Study participants and sample size

Participants will be randomly selected from both HDSS sites and will include subsistence farmers as well as children residing in their households. A farmer is defined as an individual whose primary occupation is agriculture, evidenced by the active cultivation of at least one food crop, with household livelihood primarily dependent on agricultural production.

The primary outcome variable is heart rate (beats per minute, bpm), used as a physiological proxy for heat-related strain in farmers. Heart rate reflects both physical exertion during agricultural labor and cardiovascular responses to heat stress, making it a key metric for assessing workload intensity and thermal burden. However, as heart rate increases can result from both physical exertion and heat exposure, the study will account for cardiac drift, which refers to the gradual increase in heart rate over time due to prolonged exertion in hot conditions. To differentiate between workload-related heart rate elevations and heat-induced cardiovascular strain, the following strategies will be applied:
Step data and GPS tracking will provide context for exertion levels during work activities.Time-of-day analysis will help distinguish between work-related and heat-related heart rate increases.Cross-referencing heart rate with environmental data (WBGT, temperature, humidity) will enable more precise differentiation between exertion-driven and heat-induced cardiac responses.

To estimate an appropriate sample size for the H2H pilot study, a power analysis is conducted for comparing means between two independent groups:$$n=\frac{2{\left(Z_{\alpha /2}+Z_{\beta }\right)}^{2}\times \sigma^{2}}{\delta^{2}}$$$$n=\frac{2{\left(Z_{\alpha /2}+Z_{\beta }\right)}^{2}\times \sigma^{2}}{\delta^{2}}$$

Where:
n is the sample size required per group.Z_α/2_ is the critical value associated with a desired alpha level (commonly set at 0.05 for a 95- Z_β_ is the critical value associated with the desired power of the test (commonly set at 0.80, yielding a Z_β_ value of 0.84).σ is the standard deviation of the outcome variable, which in this case is the bpm difference.δ is the expected difference in means between the two groups.

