#### Structural equation modeling (SEM) and mediation analysis

To assess both direct and indirect effects of heat exposure, the study will employ Structural Equation Modeling (SEM) with mediation analysis. This approach enables the simultaneous estimation of multiple pathways linking heat exposure to physiological stress, work capacity, harvest yields, and child nutrition, providing a comprehensive understanding of the cascading impacts of heat stress.

Direct effects will be assessed by evaluating the independent influence of heat exposure on physiological stress (e.g. heart rate, energy expenditure), work capacity (e.g. labor duration, frequency of rest breaks), and child nutritional status. These analyses will offer insights into the immediate physiological and occupational impacts of heat and their direct links to health outcomes in children.

Beyond direct effects, SEM will estimate indirect pathways through which heat exposure impacts agricultural productivity and child nutrition. The central hypothesis posits that heat exposure induces physiological stress, which subsequently reduces work capacity, leading to decreased harvest yields and, ultimately, to poorer nutritional outcomes in children. Mediation will be tested using specific pathway models, such as:
Heat exposure → Physiological stress → Reduced work capacityHeat exposure → Reduced work capacity → Lower harvest yields → Poorer child nutrition

To quantify the role of mediating variables, indirect effects (e.g. via work capacity) will be compared with total effects (the overall impact of heat exposure on child nutrition), allowing for estimation of the relative contribution of different pathways.

To ensure the validity and robustness of the SEM, model fit will be assessed using multiple indices, including the Chi-square test, Comparative Fit Index (CFI), Tucker-Lewis Index (TLI), and Root Mean Square Error of Approximation (RMSEA). Through this rigorous analytical framework, the study aims to generate reliable and generalizable evidence on how heat stress affects the livelihoods and health of subsistence farming households.

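### Adjusting heart rate for cardiac drift, which the protocol defines as arising in heat, would remove part of the heat effect that Hypothesis 1 tests if drift itself is subtracted or used as a covariate

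*Protocol article*

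**What the plan says.** Under Study participants and sample size, the protocol article states: "The primary outcome variable is heart rate (beats per minute, bpm), used as a physiological proxy for heat-related strain in farmers". Hypothesis 1 reads: "Increased heat exposure will significantly elevate physiological strain, as measured by heart rate and body temperature".

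The article recognises that heart rate rises with both work and heat. In the section on health impact pathways it promises that "careful methodological adjustments will be made to differentiate between these factors (e.g., accounting for cardiac drift in wearable device data"). Under Physiological response and work capacity, in the study procedures, it repeats that "the analysis will incorporate methodological corrections, including adjustments for cardiac drift", again in order to tell exertion from heat.

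Study participants and sample size says that drift will be accounted for and defines it as "cardiac drift, which refers to the gradual increase in heart rate over time due to prolonged exertion in hot conditions". It then lists three strategies:

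- "Step data and GPS tracking will provide context for exertion levels during work activities".
- "Time-of-day analysis will help distinguish between work-related and heat-related heart rate increases".
- Comparison of heart rate with WBGT, temperature and humidity.

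The mixed model under Work capacity and physiological response, in the data analysis, names socioeconomic status and farming intensity as example covariates. It contains no drift term.

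**The concern.** The nuisance to be removed is workload: a farmer who walks faster or lifts more has a higher heart rate at any temperature. Drift as the article defines it is a different thing, a joint product of sustained effort and heat. A quantity produced by both causes cannot separate them.

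In a model for the effect of heat on heart rate, subtracting drift or conditioning on it means conditioning on a consequence of the exposure. The part of the heat effect that appears as a progressive rise over the working day is then taken out of the estimate. The direction is known: the Hypothesis 1 effect shrinks toward zero. Any exposure-response function for physiological strain built on that estimate would be too flat.

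**Working it through.** **The passages side by side**

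1. Hypothesis 1 asks for the effect of heat on heart rate.
2. The definition of drift includes heat as a cause, so part of drift lies on the path from heat to heart rate.
3. Two sections name adjustment for drift as a means of separating exertion from heat, which treats drift as a nuisance.
4. Nowhere does the article say that the heat-driven part of drift stays in the effect, or that drift is analysed as an outcome or mediator.

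**The article's own sample size**

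Inputs from the article: δ = 5 bpm, two-sided α = 0.05 (z = 1.96), power 80% (z = 0.84), n = 63 per group. The SD is not stated. Solving the article's formula for σ at n = 63 gives about 10.0 bpm, so σ = 10 is assumed below.

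n = 2(1.96 + 0.84)² × 10² / 5² ≈ 62.8, rounded up to 63. This reproduces the stated figure. SD 9 would give 51 and SD 11 would give 76.

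**What a literal drift adjustment does**

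A simulation of 200,000 records checks the mechanism; all its settings are assumptions. The true heat effect is 5 bpm at fixed exertion and average work duration. Exertion adds 8 bpm per SD and is 0.3 SD lower in heat. Duration is uniform on 0 to 4 hours and independent of heat. A share f of the heat effect acts through drift. The estimated heat effects, in bpm, are:

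| Adjustment | f = 0 | f = 0.2 | f = 0.5 |
|---|---|---|---|
| None | 2.61 | 2.58 | 2.62 |
| Exertion | 5.02 | 4.99 | 5.03 |
| Exertion and duration | 5.01 | 4.98 | 5.01 |
| Exertion, drift subtracted | 5.01 | 3.97 | 2.51 |
| Exertion, drift as covariate | 5.01 | 3.98 | 2.49 |

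Adjusting for workload recovers the effect. Removing drift loses the fraction f. There is no loss only at f = 0, that is, when drift has no heat component, which the article's definition excludes. The unadjusted value of about 2.6 equals 5 − 0.3 × 8: it is the total effect when people also work less hard in heat, and so a different estimand.

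**Illustrative size**

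The remaining effect is 5(1 − f), and power = Φ(5(1 − f) / (10√(2/n)) − 1.96). The column for 105 per group assumes that the 210 enrolled are split equally and none is lost.

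| Share lost | Effect left (bpm) | Power, 63 per group | Power, 105 per group | n per group for 80% |
|---|---|---|---|---|
| 0 | 5.0 | 80% | 95% | 63 |
| 10% | 4.5 | 71% | 90% | 78 |
| 20% | 4.0 | 61% | 83% | 99 |
| 30% | 3.5 | 50% | 72% | 129 |
| 50% | 2.5 | 29% | 44% | 252 |

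For a 20% loss at 63 per group: 4 / (10√(2/63)) − 1.96 = 2.245 − 1.96 = 0.285, and Φ(0.285) = 0.61.

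**The case against.** The strongest reply is that adjusting for drift need not mean removing it. The article nowhere says that drift is subtracted or entered as a covariate. None of its three listed strategies removes drift, the third looks for the heat-linked part, and the mixed model has no drift term. If the authors mean only steps, GPS and time worked, nothing is lost, as the simulation shows, and a condensed article may leave the exact form to a fuller document. This stands in part: the bias is conditional. But the objection here is not to missing detail. The article names a correction and a purpose that conflict with its own definition of drift, and an analyst who follows the wording could reasonably remove drift.

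A second reply is that steps and time at work may themselves respond to heat, as Hypothesis 2 proposes, so adjusting for them also conditions on something downstream of the exposure. This stands. It is met by stating the estimand as the heat effect at a given workload, which is what separating exertion from heat implies.

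A third reply is that the power figures do not describe the Hypothesis 1 analysis. This also stands. That analysis is a repeated-measures model on continuous exposure, whereas the formula compares two independent groups.

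A reader might also infer that the first SEM path, in which "The central hypothesis posits that heat exposure induces physiological stress, which subsequently reduces work capacity", must come out with the wrong sign because working raises heart rate. The documents do not support this. They do not say that heart rate enters the SEM uncorrected, or at what lag, and nothing was calculated on the point.

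**Conclusion.** The point holds in conditional form. The article's definition makes drift partly a heat response, and its stated correction treats drift as something to be taken out when heat is to be distinguished from exertion. If drift is subtracted or used as a covariate, the Hypothesis 1 estimate is biased toward zero by the share of the effect that acts through drift. Under that reading, the direction needs no assumption beyond the article's definition.

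The size is unknown. The share is not in the documents, the SD of 10 is solved back from 63 per group, and the two-group formula is not the planned model. A fall from 80% to about 61% power for a 20% loss is therefore only an indication of scale. A reader might infer that the primary analysis is certainly biased, or that its power falls to 29%. The first goes beyond the text because the form of the adjustment is open. The second rests on a 50% share that has no source.

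**What to change.** In the section on health impact pathways, in Study participants and sample size, and in the procedures section on physiological response and work capacity, replace the adjustment for cardiac drift as follows:

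- Adjust heart rate for concurrent workload, using step count in the same interval on all days, and for hour of day. On days with GPS data, add speed and time since the start of work.
- Do not remove drift from the primary estimate. Keep the heat-by-time-at-work component as part of the reported heat effect.
- Report the drift slope as a secondary or sensitivity result on GPS days.
- State that the estimand is the heat effect on heart rate at a given workload, because workload may itself respond to heat.

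Using the same workload-adjusted heart rate as the strain mediator in the SEM is an optional step for consistency.

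The cost is a change of wording and slightly more analysis, with no new data collection. Heart rate and steps come from the same wrist device, worn throughout. GPS is assured on only 20 days of a 12-week season, or 20/84 ≈ 24% of days, so the terms that need it, and the drift slope, are limited to those days unless the trackers are carried for longer.

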#### Harvest yield (health impact pathway 3)

Remote sensing data will be used to estimate harvest yields, based on a previously developed and ground-truth validated model [31,48] in the Nouna HDSS. The remote-sensing based model will be adapted to the Kenyan context as a part of the H2H study. Specifically, Sentinel-2 satellite imagery will be processed for the growing seasons of five key crops. To monitor vegetation health and estimate household-level yields, three monthly vegetation indices will be calculated: the Normalized Difference Vegetation Index (NDVI), the Normalized Difference Red Edge Index (NDRE), and the Normalized Difference Water Index (NDWI). These indices, combined with rainfall data, will serve as input parameters for LASSO (Least Absolute Shrinkage and Selection Operator) regression models. A distinct model will be developed for each crop to generate crop-specific yield estimates. For further details, see [31].

Field boundaries will be mapped using GPS devices (Garmin Etrex 10, Garmin USA), with measurements conducted on two separate occasions per field. Field workers will accompany farmers around each field’s perimeter to ensure accurate boundary delineation. This method will enable precise estimation of household-level agricultural output by crop type, while also geolocating fields for linkage to household data.

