The fourth health impact pathway addresses the indirect consequences of heat-induced agricultural disruptions on child nutrition. Declining crop yields and increasing food insecurity may lead to dietary deficiencies, heightened undernutrition, and associated health risks in children under five. By linking environmental stressors to household food availability, this pathway seeks to quantify the nutritional and health impacts of heat exposure on vulnerable populations.

A conceptual framework (refer to Figures 1 and 2 for the conceptual framework of the H2H study and its pathways) illustrates the relationships between heat exposure, physiological strain, agricultural productivity, and child nutrition. The study will incorporate controls for potential confounders to ensure that observed effects can be robustly attributed to heat exposure rather than external factors such as soil fertility, rainfall variability, or market fluctuations.

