#### Harvest yields (health impact pathway 3)

To assess spatial variation in agricultural productivity and its relationship with heat exposure, we will conduct geospatial analyses using Geographic Information System (GIS) tools. Field boundaries – mapped via GPS – will be overlaid with remote sensing data to extract vegetation indices for each field, enabling a spatially explicit assessment of crop health and yield under varying environmental conditions.

Household-level agricultural production will be estimated using LASSO (Least Absolute Shrinkage and Selection Operator) regression models, incorporating variables such as crop type, phenological stages, and time-series vegetation indices – specifically the Normalized Difference Vegetation Index (NDVI), Normalized Difference Red Edge Index (NDRE), and Normalized Difference Water Index (NDWI) – derived from Sentinel-2 satellite imagery, as well as rainfall data from CHIRPS. To improve model robustness and prevent overfitting, five-fold cross-validation will be used to optimize model parameters and assess predictive performance.

Separate LASSO models will be developed for each major crop type, following established methods [31], thereby enhancing model specificity and improving yield forecasts at the field level. This modeling approach allows us to link remote sensing indicators to field-level agricultural output with high spatial and temporal resolution.

To evaluate the influence of heat exposure on productivity, we will identify and compare high- and low-yield regions in relation to spatial and temporal variations in temperature, integrating both indoor and outdoor temperature data. Additionally, fluctuations in temperature, humidity, and extreme weather events will be included in the analysis to assess their contributions to yield variability and to control for potential environmental confounders.

By embedding these geospatial analyses within the broader analytical framework, we aim to generate nuanced insights into how environmental stressors – particularly heat – affect agricultural output at the household level, and how this, in turn, may mediate impacts on work capacity and child nutrition.

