### Harvest yields

By integrating remote sensing techniques with a household-level crop yield model, we will generate detailed estimates of agricultural productivity across study sites. This approach allows for a fine-grained assessment of how climatic variables – including temperature, humidity, and extreme weather events – affect crop yields over time and space.

To ensure robust and context-specific yield estimations, the model will incorporate digitized field boundary data, time-series vegetation indices (e.g. NDVI, NDRE, NDWI), and rainfall patterns. Furthermore, we will evaluate the role of non-climatic factors such as soil quality, farm management practices, and seed variety selection in contributing to observed yield differences.

The analysis will offer a comprehensive understanding of the ecological and socio-economic impacts of climate change on smallholder farming systems. These insights will be critical for identifying vulnerability hotspots, developing targeted adaptation strategies, and informing evidence-based policy interventions to strengthen climate resilience among farming communities.

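### Harvest yield is a prediction from vegetation indices and rainfall, so using it as the outcome shrinks the heat effect and can shift part of it onto rain

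*Protocol article*

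**What the plan says.** All references are to the Protocol article.

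- **Source of yield.** Methods, *Harvest yield (health impact pathway 3)*: "Remote sensing data will be used to estimate harvest yields, based on a previously developed and ground-truth validated model".
- **Inputs to the yield model.** The same section names the three vegetation indices and rain: "These indices, combined with rainfall data, will serve as input parameters for LASSO (Least Absolute Shrinkage and Selection Operator) regression models". Data analysis, *Harvest yields (health impact pathway 3)*, lists crop type, phenological stage and the indices, "as well as rainfall data from CHIRPS". Expected results, *Harvest yields*: "the model will incorporate digitized field boundary data, time-series vegetation indices (e.g. NDVI, NDRE, NDWI), and rainfall patterns". None of the three names temperature.
- **Use of predicted yield as an outcome.** Data analysis, *Harvest yields (health impact pathway 3)*: "we will identify and compare high- and low-yield regions in relation to spatial and temporal variations in temperature", and "fluctuations in temperature, humidity, and extreme weather events will be included in the analysis to assess their contributions to yield variability". In *Structural equation modeling (SEM) and mediation analysis*, yield lies on the path from heat to child nutrition.
- **What the analysis should deliver.** The health impact pathways section says confounders will be controlled so that "observed effects can be robustly attributed to heat exposure rather than external factors such as soil fertility, rainfall variability, or market fluctuations". Hypothesis 3 expects heat to lower yield through farmers' work capacity and health.

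**The concern.** A fitted value responds to a driver only as far as its inputs do. Rainfall enters predicted yield directly, with its own weight. Heat can enter only through the vegetation indices, which are noisy and may miss some kinds of loss. When predicted yield is regressed on heat and rain, the heat coefficient is therefore smaller than the real effect. If rainfall is in the yield model and is correlated with heat, its weight also picks up heat damage that the indices missed.

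Three things are at stake: the heat-to-yield estimate for Hypothesis 3, the indirect path from heat through yield to child nutrition, and the exposure-response functions that Expected results offers to climate-impact models. Hypothesis 3 is the most exposed, because a crop that stands well but is harvested late or incompletely may look healthy to a satellite.

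**Working it through.** The plan states no figure to reproduce here. The structure comes from the document; **every number below is an assumption**, used to show direction and range.

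**Set-up.** Standardised heat H and rain R have correlation ρ. True yield is y = 0.40R − 0.40H + e, with Var(e) = 0.64. The vegetation index is V = y + noise with reliability r = 0.3, 0.5 or 0.7, so Var(noise) = Var(y)(1 − r)/r. All heat loss shows in the canopy.

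**Rainfall in the yield model.** The weight on V is a = Var(y|R) / (Var(y|R) + Var(noise)). The heat coefficient in predicted yield is −0.40a.

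*ρ = 0.* Var(y) = 0.16 + 0.16 + 0.64 = 0.96 and Var(y|R) = 0.80.
- r = 0.3: noise 2.24; a = 0.80/3.04 = 0.263; heat −0.11
- r = 0.5: noise 0.96; a = 0.80/1.76 = 0.455; heat −0.18
- r = 0.7: noise 0.411; a = 0.80/1.211 = 0.660; heat −0.26

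Rain is 0.40a + 0.40(1 − a) = 0.40 throughout, which is its true value.

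*ρ = −0.5.* Var(y) = 0.32 + 0.16 + 0.64 = 1.12; Var(y|R) = 0.16 × 0.75 + 0.64 = 0.76; E(y|R) = 0.60R. Rain becomes 0.40a + 0.60(1 − a) = 0.60 − 0.20a.
- r = 0.3: a = 0.76/3.373 = 0.225; heat −0.09; rain 0.555
- r = 0.5: a = 0.76/1.88 = 0.404; heat −0.16; rain 0.52
- r = 0.7: a = 0.76/1.24 = 0.613; heat −0.25; rain 0.48

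Heat is thus recovered at 22.5% to 66% of truth.

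**Rainfall left out.** Predicted yield is rV, so heat is −0.40r = −0.12/−0.20/−0.28 and rain is +0.12/+0.20/+0.28, at either correlation. Both shrink alike and nothing moves from heat to rain, but most of the shrinkage remains.

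**Which slope corrects it.** In the rainfall-free fit, observed on predicted is r·Var(y) / (r²·Var(y)/r) = 1, so it corrects nothing. Predicted on observed is r, and −0.40r / r = −0.40.

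**Heat loss only partly visible.** If half the heat effect reaches the canopy (ρ = 0), Cov(V, y) = 0.16 + 0.04 + 0.64 + 0.04 = 0.88. The corrected heat coefficient is −0.20 × 0.96/0.88 = −0.22, about half the truth. If none reaches it, the coefficient is 0 with or without rainfall in the model.

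**Check with cross-validated LASSO.** Three noisy indices, 400 training fields, 4,000 new fields, 60 repeats; true heat −0.30, rain +0.40. Recovered share of truth at ρ = 0:

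| Index noise SD | Heat loss visible | Rain in model: heat / rain | Rain out: heat / rain |
|---|---|---|---|
| 0.5 | all | 84% / 99% | 88% / 88% |
| 1 | all | 57% / 99% | 64% / 64% |
| 2 | all | 25% / 99% | 31% / 31% |
| 1 | half | 28% / 99% | 32% / 64% |
| 1 | none | 0% / 99% | 0% / 60% |

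At ρ = −0.5 with rainfall in the model, heat ran from 84% down to 0% and rain from 105% to 136%. The direction was the same in all 18 scenarios with rainfall as an input.

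**The case against.** **Rainfall is not the main cause.** This stands. Taking rainfall out moves heat only from −0.11/−0.18/−0.26 to −0.12/−0.20/−0.28 at ρ = 0. Most of the loss comes from using an imperfect prediction as the outcome.

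**A reader might infer that the rain effect is an artefact of construction.** The documents do not support that. The rain weight is learned from ground-truth yields, and with uncorrelated weather it is recovered correctly. It is inflated only when heat and rain are correlated.

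**A reader might also infer that the article promises to divide yield variation between heat and rain.** It does not. The pathways section promises control of rainfall, and the list of contributors to yield variability does not name rain. What suffers is the rain-adjusted heat coefficient on which that attribution rests.

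**Details lie elsewhere.** The analysis section introduces its inputs as examples, and the model is described in a cited paper that is not at hand. LASSO may also drop rainfall for some crops, which removes the imbalance there. Both limit the claim about rainfall. They do not touch the shrinkage, and adding temperature as an input would merely write a heat effect into the outcome in the same way.

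**The limits are acknowledged, and yield is not primary.** The Limitations section carries a general caution about LASSO assumptions and climate interactions; it does not mention rainfall serving as both input and explanatory variable. Heart rate is the primary outcome and this is a feasibility phase, which lowers the weight of the point without removing it.

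**Conclusion.** The concern holds in a limited form. Followed as written, the plan regresses a predicted yield on heat, and the heat coefficient is shrunk toward zero. A retained rainfall input adds a smaller loss, makes the heat and rain coefficients incomparable and, when the two are correlated, loads part of the heat effect onto rain. That weakens the promised attribution to heat "rather than external factors such as soil fertility, rainfall variability, or market fluctuations".

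The direction follows from the stated inputs, given indices that are imperfect and, for the rainfall part, a LASSO that keeps rain. The size cannot be fixed, because the article gives neither index accuracy, nor the heat-rain correlation, nor the share of heat loss visible in the canopy. With all heat loss visible, recovery was 22.5% to 66% under the first set of assumptions and 24% to 84% in the LASSO runs. With none visible it was 0%. A null heat-yield result would therefore not be evidence against the labour pathway of Hypothesis 3.

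**What to change.** 1. Keep the rainfall-including LASSO for forecasting.
2. For every analysis relating yield to heat or other weather, and for the structural equation model, use crop-specific LASSO yields fitted without rainfall. Enter rainfall only as a covariate.
3. Divide the weather coefficients by the slope of predicted on observed yield, estimated by cross-validation in the ground-truth data. Do not use the usual observed-on-predicted calibration slope, which is about 1. The division is exact only when the indices equal yield plus noise unrelated to weather.
4. Bootstrap the yield model so that its error reaches the intervals.
5. Report the rainfall-including version as a sensitivity analysis.
6. State that harvest loss through reduced labour that does not show in the canopy cannot be detected with this yield variable, and that a null result does not count against that pathway.

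The cost is one extra fit per crop, a resampling step, slightly lower yield prediction accuracy and wider intervals. The slope needs observed yields, so at the Kenyan site it depends on the ground-truth data used to adapt the model there. Recovering canopy-invisible loss would need measured yield in at least a subset of households; steps 1 to 6 do not provide that.
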